# Oxytocin-enhanced motivational interviewing group therapy for methamphetamine use disorder in men who have sex with men: study protocol for a randomized controlled trial

**DOI:** 10.1186/s13063-019-3225-7

**Published:** 2019-02-21

**Keywords:** Methamphetamine use disorder, Meth, Stimulant, Oxytocin, Men who have sex with men, Motivational interviewing, Group therapy, Addiction, Drug-assisted psychotherapy

## Abstract

**Background:**

The prevalence of methamphetamine use disorder (MUD) in the United States has risen dramatically in the past four decades and is concentrated in populations such as men who have sex with men (MSM). Despite the public health consequences of MUD, there are no FDA-approved psychopharmacological treatments. Psychosocial treatment alone has been shown to reduce methamphetamine use, but high attrition rates limit treatment efficacy. Promising findings from animal models of MUD using exogenous oxytocin, a social neuropeptide, have set the stage for translational work. Along with unique anti-addiction effects, oxytocin holds a primary role in enhancing social salience and modulating stress. In humans, oxytocin administration, combined with evidence-based psychosocial interventions, may act synergistically to improve addiction treatment outcomes and improve retention rates in current MUD treatment.

**Methods/design:**

We are conducting a randomized, double-blind, placebo-controlled trial of oxytocin-enhanced motivational interviewing group therapy (MIGT). Oxytocin or placebo 40 IU is administered intranasally in conjunction with six, weekly MIGT sessions. We will recruit 50 MSM, initiating treatment for MUD from specialized community health programs in San Francisco, CA, USA. Individuals will be randomized (1:1) to receive six, weekly sessions of MIGT with or without oxytocin. Our primary outcome is session attendance. Other outcomes of interest include: measures of group cohesion, anxiety, psychophysiology, and stimulant craving and use.

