The MIGT cohorts in this study will consist of two co-facilitators, one will be a licensed psychiatrist and the other will be a mental health trainee (PhD, PsyD, or psychiatry resident) along with four to six group members. All MIGT sessions will be conducted at the Alliance Health Project in San Francisco, CA, USA. A semi-structured, closed-admission, time-limited (six sessions) OE-MIGT manual for methamphetamine users was developed for this study using guidance from Wagner and Ingersoll (2013) [55]. Included are four brief psychoeducational components for optional use during the first four sessions: stages of change, ambivalence and a decisional balance chart for methamphetamine use, attachment theory and social support, and managing stress. These topics aid in the Engagement and Exploring Perspectives phases of the group, are designed to maximize the effects of intranasally administered oxytocin on MIGT for MUD, and correspond to the specific objectives of this research study. The final two sessions are left unstructured in order to allow more time for Broadening Perspectives and Moving Into Action. Adherence raters will assess session transcripts using motivational interviewing treatment integrity (MITI) 4.2; a coding system designed to measure group facilitators’ adherence to MI [56]. Consistent with previous work by the research team, a fidelity checklist reflecting the content of the session will be developed in order to determine whether the intervention was delivered as intended. Prior to participant enrollment, facilitators will receive training from an MI expert to ensure competency [57, 58].

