### Power analysis

A sample size of 25 per treatment condition will provide us with > 99% power to detect an effect size comparable to the large between-condition effect size (*d* = 1.44) observed for attendance from our preliminary 3-week trial in cocaine users [53] with a two-tailed alpha = 0.05. In addition, this sample size will provide 80% power to detect an effect size of 0.81 or greater.

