### Setting and study population

Previous evidence suggests that oxytocin administration may lead to different outcomes based on the gender [59] and sexual orientation [60] of recipients. To control for this, we limited study participation to men who have sex with men (MSM). Fifty MSM who meet the criteria for MUD will be enrolled in the current study. Participants will be recruited from community mental health programs specializing in this clinical population in San Francisco, CA, USA, including the San Francisco AIDS Foundation, the Alliance Health Project, the Positive Health Program HIV/AIDS Clinic, as well as from study flyers posted in the community. Due to the specificity of our patient population, we acknowledge that participants may recognize each other or even belong to the same social circles. While we do not formally measure pre-existing relationships among those assigned to the same therapy cohort, we do take steps to ensure that intimate partners are not assigned to the same therapy cohort by collecting names of intimate partners as well as any community member that each potential participant would *not* want to be enrolled with in group therapy.

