### Procedure

Eligible individuals enrolled in the study will be randomized, using a computer-generated random number sequence, to receive MIGT along with either oxytocin or placebo administration prior to each session. Each member of a specific MIGT cohort will receive the same study drug as the other members of that cohort, and members of each MIGT cohort will receive the same study drug for all six sessions. Blinding procedures will be controlled by Wellspring Compounding Pharmacy (Berkeley, CA, USA).

Previous work has shown that intranasal oxytocin administration begins to have physiological effects within 30 min and lasts for at least 90 min [35]. Thirty minutes prior to beginning each MIGT session, the study physician will administer the study drug (Wellspring Compounding Pharmacy, Berkeley, CA, USA) intranasally using a mucosal atomization device (MAD300; Teleflex technologies, Mooresville, NC, USA) attached to a 1-mL Luer-lock syringe. The oxytocin will be prepared as 40 International Units (IU) of oxytocin per 1 mL. Participants will receive 1 mL total, with 0.5 mL administered in each nostril using two separate syringes (with 0.06 mL additional drug in the first syringe to account for the MAD300 dead space). The administration procedures are consistent with recommendations for standardized intranasal drug administration [64]. Study drug administration will occur with all members present in the group therapy space, and the order of administration to individuals within a cohort will be randomized at each session.

To test tolerability to the study drug, participants will complete an Oxytocin Side Effect Checklist (OTSE), a list of 21 possible side effects [37] and the opportunity to report any other adverse effects, after each MIGT session. In addition, participants will be asked after each session to guess whether they have received oxytocin or placebo.

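### The article says individuals are randomised 1:1 but gives one drug to each closed therapy cohort, so the unit of randomisation is unclear; the power statement counts 50 independent men.

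*Protocol article*

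**What the plan says.** All references are to the protocol article.

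- **Abstract, Methods/design:** "Individuals will be randomized (1:1) to receive six, weekly sessions of MIGT with or without oxytocin".
- **Procedure:** "Eligible individuals enrolled in the study will be randomized, using a computer-generated random number sequence". The next sentence reads "Each member of a specific MIGT cohort will receive the same study drug as the other members of that cohort", and the drug stays the same for all six sessions.
- **Motivational interviewing group therapy (MIGT):** groups are closed to new members once started, with two co-facilitators "along with four to six group members".
- **Setting and study population:** "Fifty MSM who meet the criteria for MUD will be enrolled in the current study". Cohort membership is also constrained by "collecting names of intimate partners as well as any community member that each potential participant would" not wish to share a group with.
- **Power analysis:** "A sample size of 25 per treatment condition will provide us with > 99% power to detect an effect size" of d = 1.44, the value "observed for attendance from our preliminary 3-week trial in cocaine users". The same sample size is said to give 80% power at d = 0.81, two-sided alpha 0.05.
- **Data Analysis Plan:** attendance is compared by generalized estimating equations that correct for repeated observations on a man and for cohort membership.
- **Limitations:** group therapy is acknowledged to complicate the analysis, probably at a cost in power.

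**The concern.** The text names the individual as the unit of randomisation and then describes a treatment fixed at cohort level. Two different trials fit these sentences.

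- **Cohorts formed, then allocated.** This is a cluster-randomised trial with a small number of units. The abstract and the Procedure then misstate what is randomised, and balance between arms depends on how a short list of cohorts was drawn up.
- **Men allocated, then grouped.** This is an individually randomised trial with group-delivered treatment. Each man must wait for a closed group in his own arm, and the keep-apart names have to be honoured after his arm is fixed. Losses while waiting fall after randomisation. The primary outcome is attendance, and the Background cites attrition of 60% or more, so the point from which losses are counted matters.

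A reader needs to know which trial this is in order to judge allocation, count losses and interpret the power statement.

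**Working it through.** **Inputs from the article.** N = 50, 25 per arm; cohort size 4 to 6; d = 1.44 and d = 0.81; two-sided alpha 0.05. **Assumed.** Ten cohorts of five (the midpoint of 4 to 6) and an intracluster correlation (ICC) of 0 to 0.20. The article gives no ICC.

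**1. The plan's own figures.** Two-sample t-test, noncentrality d × √(n₁n₂/(n₁+n₂)), 48 df. With 25 v 25 the multiplier is √12.5 = 3.536.
- d = 1.44: noncentrality 5.09, power 99.9% (stated: above 99%).
- d = 0.81: noncentrality 2.86, power 80.1% (stated: 80%).

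Both reproduce, with 50 independent men and no allowance for cohorts.

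**2. Number of cohorts.** 50/6 = 8.3 and 50/4 = 12.5, so about 9 to 13 (13 only if one starts with fewer than four men); 10 at the midpoint.

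**3. Power with clustering, 5:5 split.** Design effect = 1 + (5 − 1) × ICC. Noncentrality = d × √(n₁n₂/(50 × design effect)), on 10 − 2 = 8 df. For ICC 0.10 and d = 0.81: 0.81 × √(625/(50 × 1.4)) = 2.42, against a critical t of 2.306, giving 57%.

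| ICC (assumed) | Design effect | Power, d = 0.81 | Power, d = 1.44 |
|---|---|---|---|
| 0 | 1.0 | 71% | 99% |
| 0.05 | 1.2 | 63% | 98% |
| 0.10 | 1.4 | 57% | 96% |
| 0.20 | 1.8 | 47% | 91% |

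The drop from 80% to 71% at ICC 0 comes only from having 8 rather than 48 df.

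**4. Balance, if 10 cohorts were allocated by simple randomisation.** Binomial(10, 0.5):
- P(5:5) = 252/1024 = 24.6%.
- P(7:3 or more extreme) = 2 × (120 + 45 + 10 + 1)/1024 = 352/1024 = 34.4%.

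If instead 50 men were allocated by simple randomisation, 70:30 or worse has probability 0.7%.

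**5. What imbalance costs.** Formula of step 3, ICC 0.10, 8 df, arms of 5a and 5b men.

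| Cohort split | Men | Power, d = 0.81 | Power, d = 1.44 |
|---|---|---|---|
| 5:5 | 25 v 25 | 57% | 96% |
| 6:4 | 30 v 20 | 55% | 96% |
| 7:3 | 35 v 15 | 50% | 93% |
| 8:2 | 40 v 10 | 40% | 85% |

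At d = 0.81 imbalance costs about 2 points at 6:4 and 7 at 7:3. The fall from 80% to 57% is already there at a perfect 5:5 split.

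These are t-test approximations on the article's effect-size scale. They are not a simulation of the planned binary model.

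**The case against.** Four stronger readings are tempting, and the article supports none of them.

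- **That the sequence is unrestricted.** The text says only that it is computer-generated. That fits a permuted-block list as well as simple randomisation, and the 1:1 ratio and 25 per condition fit a restricted list. An article commonly leaves such detail to the full protocol, so its absence is not a defect. The 25% and 34% figures hold only if allocation was simple and by cohort.
- **That the two statements flatly contradict each other.** Men can be randomised and then placed in single-drug groups. Fifty units are then allocated, and the ten-unit balance calculation does not apply. The waiting losses and keep-apart exclusions of that route follow from its logic; the article does not describe them.
- **That the planned analysis ignores the design.** It does not: the Data Analysis Plan corrects for cohort membership, and the Limitations concede a loss of power.
- **That imbalance is the main threat to power.** Most of the loss comes from clustering and few degrees of freedom, which blocking would not recover. At d = 1.44, the effect the trial was sized on, power stays at 93% or more down to 7:3 with ICC 0.10.

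These objections narrow the point but leave the unit of allocation unresolved. The Power analysis section also still carries no allowance for the clustering that two other sections acknowledge.

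**Conclusion.** The point holds in limited form. The unit of randomisation, a basic design fact, is stated as the individual and implied to be the cohort, and the article does not settle which. The power statement is arithmetically right but only for 50 independent men.

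The consequence depends on the effect. At the protocol's detectable effect of 0.81, 80% becomes 47% to 71% for ICCs of 0.20 down to 0, assuming 10 equal cohorts split evenly and 8 df. At d = 1.44 power is still 91% to 99%. Imbalance is secondary and conditional on simple allocation of cohorts. This should be corrected, but it does not by itself invalidate the planned comparison.

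**What to change.** Reconcile the abstract and the Procedure section so that both name the same unit.

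- **If the unit is the cohort:** describe the trial as cluster-randomised. State that each cohort is filled and closed, with the keep-apart names applied, before it is allocated. Allocate any remaining cohorts from a concealed restricted list, for example permuted blocks of cohorts. Restate the Power analysis for cohorts over a range of ICC.
- **If men were allocated and then grouped:** say so, describe an individually randomised group-treatment trial, and count losses from the point of allocation. Outcomes are still shared within groups, so the power statement should allow for clustering here too.

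The cost is a short clarification, a revised power paragraph and, if cohorts remain to be formed, a new list at the pharmacy. Small blocks are slightly predictable, though the double-blind design limits the harm. The Trial status section puts the end of recruitment at about 31 December 2018, before publication on 21 February 2019. If recruitment is complete, only the description, power statement and reporting can change.

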**Discussion:**

This will be the first study of oxytocin’s effects in humans with MUD. Findings from this novel protocol will attempt to bridge existing animal data with the need for innovative clinical treatments for MUD, inform the growing field of pharmacologically-enhanced psychotherapy, and help to elucidate mechanisms behind oxytocin’s potential anti-addiction effects.

**Trial registration:**

ClinicalTrials.gov, ID: NCT02881177. Registered on 26 August 2016.

**Electronic supplementary material:**

The online version of this article (10.1186/s13063-019-3225-7) contains supplementary material, which is available to authorized users.

## Background

Methamphetamine is a potent psychostimulant with high abuse potential [1]. Methamphetamine and amphetamine-type stimulants are second only to cannabis as the most frequently used illicit substance worldwide [2], and, according to the 2017 Global Drug Survey [3], methamphetamine was the illicit substance most likely to lead to emergency medical treatment seeking. High healthcare utilization contributes to the multifactorial economic burden of methamphetamine, which is estimated to be upwards of US$23.4 billion in the United States (US) alone (Rand Corporation, 2008). The prevalence of methamphetamine use disorder (MUD) in the US has risen dramatically in the past four decades, with high concentrations among men who have sex with men (MSM) [4–6]. Despite the personal and societal consequences of methamphetamine use, no pharmacological agent currently has an FDA-designated indication to treat MUD [7, 8].

Psychosocial treatment alone has been shown to reduce methamphetamine use and rates of relapse, with a longer duration of treatment producing better results [9–13]. However, methamphetamine users exhibit high attrition rates of 60% or more, which limits the effectiveness of treatment and leads to missing data and validity issues in clinical research contexts [14]. This complicates efforts to identify pharmacotherapy candidates or to improve evidence-based psychosocial treatments for MUD [8, 15]. Methamphetamine is associated with impairments in social cognition and theory of mind, including a hypersensitivity to social threat, which likely contribute to reduced treatment adherence and retention [16–19]. Social rehabilitation, often in the form of group and family therapy, is a prominent component of gold-standard psychosocial treatments for MUD [20, 21]. Even in animal models of methamphetamine addiction, socially housed—versus individually housed—rats were protected against escalating methamphetamine self-administration [22]. Given the social complexities and challenges surrounding MUD clinical treatment and research, an adjunctive pharmacotherapy that might enhance social cognition and boost engagement and retention in effective psychosocial treatment could greatly improve outcomes [23].

Oxytocin, a hypothalamic peptide that plays a critical role in mammalian attachment and affiliative behavior [24–26], administered exogenously, is a promising candidate as an adjunctive addiction treatment [27, 28]. Oxytocin has unique anti-addiction effects [27, 29] along with social salience [30] and stress-tempering properties [31–33], which together may shift attentional bias toward positive social reward at the expense of conditioned drug-related reward [28, 34]. Oxytocin is a large, hydrophilic molecule, so does not readily cross the blood-brain barrier after peripheral administration. The intranasal route is thus far the most efficient way to deliver oxytocin to the human central nervous system [35, 36] and is extremely safe and tolerable [37]. What is more, there are no discernable subjective effects (i.e., research participants cannot typically guess whether they have received oxytocin versus placebo), which allows the use of an inactive placebo [37].

Methamphetamine self-administration in rats has been shown to dysregulate the oxytocin system [38–40], and some evidence for this exists in humans [41]. In animal models of methamphetamine addiction, oxytocin administration reduces the acquisition and increases extinction of compulsive methamphetamine self-administration and reduces stress-primed and drug-primed reinstatement of methamphetamine-seeking behavior [27, 42–47]. In addition, oxytocin administration attenuates methamphetamine tolerance and withdrawal, methamphetamine-induced stereotyped movements, methamphetamine-induced conditioned place preference, and reduces methamphetamine-induced c-Fos expression in areas of the basal ganglia implicated in addiction [44, 48–51]. In humans, oxytocin has demonstrated some efficacy in early trials with alcohol, cannabis, opioid, and cocaine users [52, 53]. To our knowledge, this will be the first study to investigate the effects of intranasally administered oxytocin on the symptoms of MUD in humans.

Oxytocin administration in combination with evidence-based group psychotherapy—oxytocin-enhanced motivational interviewing group therapy (OE-MIGT)—may synergistically enhance treatment outcomes and address the notoriously high drop-out rates evident in MUD populations. We aim to investigate the effectiveness of intranasally administered oxytocin on MIGT treatment engagement. Specifically, we hypothesize that oxytocin will increase attendance at treatment sessions. In addition, we will estimate effect sizes and assess procedures used to test oxytocin’s effects on group cohesion, anxiety, psychophysiological stress reactivity, and stimulant craving and use for future trials. This novel translational protocol attempts to bridge ample animal data with the need for innovative clinical treatments for MUD.

## Methods/design

### Study design

This is a randomized, double-blind, placebo-controlled study of OE-MIGT. Specifically, intranasally administered oxytocin or placebo will be administered in conjunction with each of six, weekly, 90-min MIGT sessions.

### Motivational interviewing group therapy (MIGT)

Motivational interviewing (MI) is defined as a “collaborative conversation style for strengthening a person’s own motivation and commitment to change” a behavior [54], be it increasing engagement in treatment or discontinuing or cutting down methamphetamine use. MI is client-centered; as a result, the client generates any and all treatment goals and the personalized plans for attaining them. When conducting MI in group settings, co-facilitators use MI-consistent techniques (open-ended questions, affirmations, reflections, and summarization) in the context of the spirit of MI (one of collaboration, compassion, acceptance, and evocation) in order to foster healthy interactions among members and co-facilitators that are focused on exploring healthy behavior change. MIGT co-facilitators aim to guide members through four general group phases: (1) Engagement – enlist members to “open up” by involving them in meaningful relationships based in understanding and acceptance, (2) Exploring Perspectives – collaboratively, and strategically, narrow the focus from cohesion-building to members’ perspectives about their current situations, (3) Broadening Perspectives – elicit perspectives and ideas about change, motivation to change, and hopes for success, and (4) Moving Into Action – develop specific plans for *how to* implement change [55]. In this way, MIGT can improve personal recognition of ambivalence, support autonomy, increase motivation and commitment to change, and improve treatment engagement and participation [55].

The MIGT cohorts in this study will consist of two co-facilitators, one will be a licensed psychiatrist and the other will be a mental health trainee (PhD, PsyD, or psychiatry resident) along with four to six group members. All MIGT sessions will be conducted at the Alliance Health Project in San Francisco, CA, USA. A semi-structured, closed-admission, time-limited (six sessions) OE-MIGT manual for methamphetamine users was developed for this study using guidance from Wagner and Ingersoll (2013) [55]. Included are four brief psychoeducational components for optional use during the first four sessions: stages of change, ambivalence and a decisional balance chart for methamphetamine use, attachment theory and social support, and managing stress. These topics aid in the Engagement and Exploring Perspectives phases of the group, are designed to maximize the effects of intranasally administered oxytocin on MIGT for MUD, and correspond to the specific objectives of this research study. The final two sessions are left unstructured in order to allow more time for Broadening Perspectives and Moving Into Action. Adherence raters will assess session transcripts using motivational interviewing treatment integrity (MITI) 4.2; a coding system designed to measure group facilitators’ adherence to MI [56]. Consistent with previous work by the research team, a fidelity checklist reflecting the content of the session will be developed in order to determine whether the intervention was delivered as intended. Prior to participant enrollment, facilitators will receive training from an MI expert to ensure competency [57, 58].

